## Objectives

The primary objective of this study is to evaluate the percentage of all HF subjects with an improvement in a clinical composite score (CCS) from pre-CRT implant to 12 months. Subjects will be stratified by paroxysmal, persistent, and long-standing persistent AF subtypes implanted with a 2-lead CRT-DX system.

Secondary objectives include the following: (1) to evaluate the rate of composite all-cause death and HF hospitalizations through 12 months; (2) to compare AF subtypes for CCS status, changes in Atrial Fibrillation Effect on Quality-of-Life Questionnaire, changes in Minnesota Living with Heart Failure Questionnaire, changes in NYHA, changes in 6-minute walk test, and changes in AF burden at 6 and 12 months; (3) to evaluate the proportion of subjects showing improvement from pre-CRT using a CCS at 6 months; (4) to evaluate the observed major complication rates from device implantation in this population at 12 months; (5) to evaluate the percentage of subjects converting to sinus rhythm at any time during the 12-month follow-up period, along with reason for conversion, both overall and by AF subtype.

## Design

### General considerations

The BIO-AffectDX Study is a multicenter, prospective, observational, single-arm study designed to evaluate the rate of subjects showing improvement from pre-CRT using a CCS at 12 months in up to 400 HF subjects with paroxysmal, persistent, or long-standing persistent AF subtypes and a 2-lead CRT-DX system. This study is an industry-initiated clinical trial designed by a steering committee consisting of physicians (who also serve as investigators) in collaboration with the sponsor. Study subjects will be enrolled at up to 50 participating US sites. Target enrollment percentages are 50%, 30%, and 20% of the total study population for paroxysmal, persistent, and long-standing persistent AF, respectively. Patients will be screened for the inclusion and exclusion criteria and sign an informed consent prior to baseline assessments, which include quality-of-life assessment, 6-minute walk test, NYHA class assessment, rhythm collection, and pertinent medical history. Subjects will be implanted with a CRT-DX (BIOTRONIK SE & Co KG, Berlin, Germany) pulse generator and DX ICD (BIOTRONIK SE & Co KG) lead, plus an LV lead within 30 days following informed consent. All subjects eligible for the study will receive a new (de novo) implant or undergo an upgrade from an existing single-chamber ICD system that includes a DX ICD lead. Subjects will be seen for follow-up visits at 3, 6, and 12 months postimplant. In addition, details on ablation or cardioversion procedures occurring during follow-up will be collected, which include recording atrial rhythm pre- and postprocedure, the cardioversion and catheter ablation procedure date, type and success as determined by the investigator, and device programming and settings, as well as device diagnostics, electrical parameters, and programmed parameters. HF, all-cause mortality, and arrhythmia events will be collected and adjudicated by independent event committees. All-cause death and HF hospitalization among all subjects will be calculated as raw number and percentage of subjects at 12 months. Mortality will be assessed by each site by a thorough review utilizing all available medical records. HF events will include HF hospitalization and worsening HF events without hospitalization. Adjudicated arrhythmic events will be limited to device-classified ventricular tachycardia (VT) and ventricular fibrillation (VF) episodes with shock treatment. Device-classified VT and VF episodes with antitachycardia pacing but no shock that transmitted and are available on home monitoring will also be adjudicated. Study results will be hypothesis generating, given the observational design of the study without use of a prospective control arm.

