### Follow-up

Following patient consent and the implantation procedure, subjects will be evaluated during in-office follow-up visits at 3, 6, and 12-month postimplant. Subject assessments at each visit will include an Atrial Fibrillation Effect on Quality of Life questionnaire, Minnesota Living with Heart Failure Questionnaire, and an NYHA class assessment. In addition, a Patient Global Assessment (PGA) will be given to collect the patient’s reported rating of overall health at each follow-up compared to prior to receiving the CRT system. Subject responses to the PGA are captured on a scale of 7 responses, from Markedly Better to Markedly Worse. Additionally, at the 6- and 12-month visits a 6-minute walk test will be administered. After completion of subject assessments, a routine device interrogation, review of all stored device-classified VT and VF shock intracardiac electrograms, and cardiovascular and oral anticoagulation medication reconciliation will occur. An evaluation of current atrial rhythm via a standard method (3-lead, 5-lead, 12-lead, programmer strip, etc) will also be collected. Echocardiography data will be obtained and analyzed for subjects with routine echocardiography testing data available both at baseline and 12-month follow-up. Some of the echocardiography data of interest will include left atrial size and LV dimensions and degree of mitral regurgitation in addition to other clinically relevant parameters. Adverse events including HF, arrhythmia, and death events will be collected at each visit.

Telehealth follow-up visits are replacing in-office follow-up visits in many centers. While the BIO-AffectDX Study strongly recommends an in-office visit whenever possible, telehealth visits in conjunction with a live phone or video call between the subject and investigational site staff are allowed. As conventional methods used to obtain a subject’s cardiac rhythm status are not available during a telehealth follow-up visit, an on-demand remote device data download will be used to provide current rhythm status for the subject.

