### Data analysis

For all study objectives and any additional data of interest collected, descriptive statistics will be used to present and summarize the data collected during the study.

Frequency distributions and cross-tabulations will be presented for discrete variables. Means, standard errors, and ranges will be presented for continuous variables.

The primary objective of this study is to evaluate the number and percentage of all HF patients with paroxysmal, persistent, and long-standing persistent AF subtypes showing improvement from baseline at 12 months. A CCS based on changes in NYHA class, PGA status, HF hospitalization status, and all-cause death is utilized to define the primary objective. The primary objective will be assessed by performing an exact point estimate and 1-sided upper 95% confidence interval for the rate of improvement.

The CCS employs a hierarchical method to classify each subject with a status of “Improved,” “Worsened,” or “Unchanged.” A patient is classified as “Worsened” if they have experienced death due to any cause, a HF hospitalization, a moderate or marked worsening in PGA, or worsening of NYHA functional class compared to baseline. A patient is considered “Improved” if they improved in at least 1 of the NYHA or PGA and did not worsen in any component. All other patients are classified as “Unchanged.” The hierarchy to determine CCS classification is displayed in Figure 2. The PGA will ask subjects to assess how their overall status has changed since prior to receiving CRT therapy.^27^^,^^28^

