**Figure 2 fig2:**
[figure not shown]
Hierarchy of clinical composite score. NYHA = New York Heart Association classification; PGA = Patient Global Assessment.

In the BIO-AffectDX study, subjects will be analyzed on both an intention-to-treat and an as-treated basis to account for removal or exchange of the implanted CRT-DX device system. The primary analysis for the primary objective will include the entire cohort, including all AF subtypes. Secondary objective analysis for each AF subtype (ie, paroxysmal AF, persistent AF, and long-standing persistent AF) subgroup will utilize the subtype documented at the baseline medical history collection using the intention-to-treat population.

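### The 12-month death or HF-hospitalization rate is fixed as a raw percentage of all subjects, which understates the risk when subjects leave early without an event

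*Protocol article*

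**What the plan says.** The first secondary objective (Objectives) is "to evaluate the rate of composite all-cause death and HF hospitalizations through 12 months". The estimator is in General considerations: "All-cause death and HF hospitalization among all subjects will be calculated as raw number and percentage of subjects at 12 months". No allowance for incomplete follow-up is attached to that sentence. The same section says that sites establish mortality by searching the medical records they can reach. It says nothing comparable for HF hospitalizations.

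The primary outcome is the CCS, defined under Data analysis. The class *Worsened* is given to subjects "if they have experienced death due to any cause, a HF hospitalization, a moderate or marked worsening in PGA, or worsening of NYHA functional class" relative to baseline, and *Improved* to subjects "if they improved in at least 1 of the NYHA or PGA and did not worsen in any component". For the rest: "All other patients are classified as" *Unchanged*. The paragraph under Figure 2 adds: "The primary analysis for the primary objective will include the entire cohort, including all AF subtypes". NYHA and PGA are collected more than once, because "subjects will be evaluated during in-office follow-up visits at 3, 6, and 12-month postimplant" (Follow-up).

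Subjects who leave before implant, or are not implanted within 30 days of consent, are screen failures and outside the analysis population. The text shown gives no rule for a subject who is implanted and then leaves before 12 months.

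**The concern.** A rate through 12 months is a risk over a fixed period. A raw percentage estimates it without bias only if everyone is followed for the whole period or has the event first. A subject lost at month 2 without an event stays in the denominator for the year and can no longer add to the numerator, so ten unobserved months are treated as observed and event-free. A low event rate makes the device look better. The article also foresees comparison with published rates or with a sinus-rhythm CRT-D group, where unequal follow-up would distort a raw rate.

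The CCS raises a related, weaker question. The residual class takes everyone who is neither *Worsened* nor *Improved*, and the primary analysis takes the entire cohort. Applied to the letter, a subject with no event and no post-implant NYHA or PGA would be reported as if observed not to have changed. That subject's status is unknown.

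**Working it through.** **Inputs.** The article states no expected event rate and no dropout rate, so it has no figure of its own to reproduce here. Assumed:
- true 12-month composite risk F = 20% (range 10% to 25%);
- fraction leaving d = 10% to 20% (range 5% to 20%), with exits uniform over the year;
- exponential event times, and no events seen after exit.

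From the article: n = 400 and the normal-approximation interval under Sample size justification.

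**Event rate, leaving unrelated to risk.**
- Hazard: λ = −ln(1 − F) = −ln(0.80) = 0.2231 per year.
- Average chance that a leaver's event is seen before exit: 1 − F/λ = 1 − 0.20/0.2231 = 0.1037.
- Expected raw rate: (1 − d) × F + d × 0.1037.

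| d | Calculation | Raw rate |
|---|---|---|
| 5% | 0.95 × 0.20 + 0.05 × 0.1037 | 19.5% |
| 10% | 0.90 × 0.20 + 0.10 × 0.1037 | 19.0% |
| 15% | 0.85 × 0.20 + 0.15 × 0.1037 | 18.6% |
| 20% | 0.80 × 0.20 + 0.20 × 0.1037 | 18.1% |

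Over F = 10% to 25% and d = 5% to 20%, the shortfall is 0.2 to 2.4 points. In a simulation of 4,000 studies of 400 subjects (F = 20%, d = 10%), the raw percentage averaged 19.0% and 1 minus Kaplan-Meier averaged 20.0%.

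For scale, the 95% half-width at 20% and n = 400 is 1.96 × √(0.20 × 0.80/400) = 3.9 points.

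**Event rate, leavers at twice the hazard (d = 10%).**
- Leavers' true risk: 1 − 0.80² = 0.36.
- True overall risk: 0.90 × 0.20 + 0.10 × 0.36 = 21.6%.
- Leavers' observed risk: 1 − 0.36/(2 × 0.2231) = 0.193.
- Raw rate: 0.18 + 0.10 × 0.193 = 19.9%.
- Kaplan-Meier removes only part of this gap. The hazard among those at risk at time t is λ(1 + w(t)), where w(t) is the leavers' share of the risk set: 0.1(1 − t)e^(−2λt) divided by 0.9e^(−λt) + 0.1(1 − t)e^(−2λt). Integrating w from 0 to 1 gives 0.048, so the estimate tends to 1 − exp(−0.2231 × 1.048) = 20.9%.

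**CCS.** Assume 60% improved among those assessed, a fraction m = 10% unassessed and all placed in *Unchanged*, and a proportion q of the unassessed who would have improved.
- Reported: (1 − m) × 0.60 = 0.90 × 0.60 = 54%.
- True: 0.54 + 0.10 × q, so the shortfall is m × q.
- q = 60%: 6 points. q = 30%: 3 points. q = 0: none.

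The half-width at 60% and n = 400 is 1.96 × √(0.60 × 0.40/400) = 4.8 points.

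**The case against.** The study is descriptive and labelled hypothesis generating, has no formal test of the primary objective, and treats its secondary analyses as exploratory. A count and percentage is a legitimate descriptive summary, and nothing forbids a Kaplan-Meier estimate beside it. The assumed bias of 1 to 2 points is smaller than the 3.9-point half-width. Record review may find deaths after exit, and telehealth visits may reduce missed assessments. All of this limits the size of the problem. It does not remove it: the article names an estimator and a denominator, an analysis plan that used censoring would depart from that sentence, and description is the study's whole output.

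The objection is stronger on the CCS. The definition does not say what happens when the 12-month NYHA or PGA is missing, and such rules commonly sit in a full protocol or analysis plan, neither of which is shown. An event before exit already gives *Worsened*. If a 3- or 6-month status were carried forward, a leaver could count as *Improved* and the bias could run upward.

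A reader might therefore infer more than the document supports:
- *Both rates are necessarily too low.* This does not follow for the improved rate, whose bias depends on an unstated rule and on how leavers would have fared.
- *The 12-month complication rate has the same flaw.* The sentence on the raw percentage covers death and HF hospitalization only, and no estimator is stated for complications.
- *The AF-subtype objective is distorted through this composite.* The second secondary objective does not list the composite, so it would be compared by subtype only in exploratory subgroup analyses.

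**Conclusion.** The point on the event rate holds. As specified, the raw percentage counts unobserved time after exit as event-free and understates the 12-month composite risk if subjects leave early. The size is modest: 1.0 to 1.9 points at an assumed true 20% with 10% to 20% uniform, non-informative dropout. It would be larger if leavers are at higher risk, smaller if records capture deaths after exit, and nil with complete follow-up.

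The CCS point is secondary and rests on a literal reading of the residual class together with the whole-cohort analysis. If that reading is applied, the improved rate falls short by 0 to 6 points at 10% missing and an assumed 60% improved. Six points is the maximum under those assumptions and requires leavers to improve as often as completers. An understated improved rate would be conservative, whereas an understated event rate favours the device.

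**What to change.** 1. Report the composite of death and HF hospitalization as 1 minus the Kaplan-Meier estimate at 12 months with a 95% confidence interval. Censor event-free subjects at last contact, and keep the raw counts beside it.
2. State the number of subjects who left before 12 months. Note that Kaplan-Meier assumes leaving is unrelated to risk.
3. In the CCS, limit *Unchanged* to subjects actually assessed at 12 months. Classify death and HF hospitalization regardless of visits. State a rule for a missing 12-month status, and show missing counted as not improved as a lower bound for the improved rate.

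The cost is a few sentences of analysis text and standard procedures in the SAS version already planned. No new data should be needed, since a rate through 12 months already requires events to be placed in time and the events are adjudicated. The downside is a slightly less favourable event rate.

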
### Sample size justification

There is no formal inferential analysis scheduled for the primary objective. The study was designed to limit the number of subjects involved, while still providing CRT-DX therapy to a sufficiently large subject population to ensure a representative and statistically meaningful sample. It is anticipated that at least 400 subjects will be implanted and followed through 12 months postimplantation at up to 50 US sites. The sample size required to assess the primary objective is based on the precision of improvement from baseline achieved using an exact point estimate and 1-sided upper 95% confidence interval. The sample size for the primary objective was calculated based on the following assumptions:

The standard normal approximation to the 95% confidence interval associated with an estimate of a binomial parameter (p) is given by:

95% Confidence Interval: p ± 1.96 [ p (1 − p) / n ]^1/2^

To meet the enrollment goals for the BIO-AffectDX study, target enrollment percentages within each AF subtype and based on prior use of CRT-DX systems are defined as 50%, 30%, and 20% of the total study population for paroxysmal, persistent, and long-standing persistent AF, respectively. Therefore, it is expected that no single AF subtype will be greater than 60% of the total study population.

A limitation of using the above method is that secondary and subanalyses are exploratory and will not be adequately powered. This will be mentioned in all results, with confidence intervals and effect sizes also given to provide complete transparency, with a clear distinction that owing to small samples, the results likely overestimate the true effect size in the population.

### Eligibility

Subjects will be eligible for enrollment if they meet the standard CRT-D indication according to current guidelines and have a documented history of paroxysmal, persistent, or long-standing persistent AF. Paroxysmal AF will be defined as AF that terminates spontaneously, or with intervention within 7 days. Persistent-continuous AF will be defined as sustained AF beyond 7 days. Long-standing persistent-continuous AF will be defined as AF of greater than 12 months in duration. The full list of eligibility criteria is summarized in Table 1.

**Table 1 tbl1:** Study eligibility criteria

Inclusion criteria	• Standard CRT-D indication according to current guidelines • Patient has documented history of paroxysmal, persistent, or long-standing persistent AF • De novo implant or upgrade from a DX ICD system • Implant planned to occur no more than 30 days after signing consent • Patient is able to understand English or Spanish • Patient is able to understand the nature of the study and provide informed consent • Patient is willing and able to complete all routine study visits at the investigational site for up to 12 months of follow-up • Patient is willing to utilize BIOTRONIK Home Monitoring® via CardioMessenger • Patient age is greater than or equal to 18 years or older
Inclusion criteria after consent has been obtained	• Baseline subject assessment is evaluated as NYHA class II, III, or ambulatory IV heart failure at study enrollment visit • Baseline subject assessment of 6-minute walk test is completed at study enrollment visit and walk distance ≤450 meters (1476 feet)
Exclusion criteria	• Contraindication to CRT-D/CRT-DX • Patient has current or previous atrial pacing need • Patient is considered for a His bundle pacing system • Patient has current or previous pacemaker, non-DX ICD implant, or biventricular pacing system prior to enrolling • Patient is currently planned for a PVI catheter ablation procedure within 3 months of consent • Patient life expectancy is less than 1 year • Patient is expected to receive heart transplantation or ventricular assist device within 1 year after implant

AF = atrial fibrillation; CRT = cardiac resynchronization therapy; ICD = implantable cardioverter-defibrillator; PVI = pulmonary vein isolation.

### Protection of human rights, recruitment, and consent

Institutional Review Board approval is required from each institution prior to participation in this clinical study. Written informed consent will be obtained from the patient prior to collection of any study-specific data.

Consented subjects will be considered provisionally enrolled until a CRT-DX is implanted successfully. Subjects with both signed informed consent and an implanted CRT-DX system are considered enrolled. Provisionally enrolled subjects that exit prior to implant or do not receive a CRT-DX system within 30 days of signing consent will be considered screen failures, and will not be included in the analysis population or count toward the 400-subject enrollment goal.

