### Device implantation

Patients will be implanted with a CRT-DX system according to current clinical standards, based on current guideline-based clinical indications for a CRT-D. Implantation with a CRT-DX system can take place no more than 30 days after consent. The CRT-DX system will be determined by the site investigator to be a successful implantation of the CRT-DX pulse generator, a DX ICD lead, and a quadripolar LV lead. A CRT-DX system is considered “unsuccessful” if any component of the CRT-DX system (CRT-DX pulse generator, DX ICD lead, and LV lead) is attempted to be implanted but could not be placed in a stable position, or if the CRT-DX system is unable to deliver adequate therapy owing to any cause attributable to the implant procedure as determined by the investigator. Additionally, geographic location of the atrial dipole within the atrium will be assessed visually by the site investigators. The anatomic locations within the atrium will be characterized at the time of implant as upper third, mid third, lower third, or unknown. Lead implantation and implant approaches will be performed according to institutional standard procedures of the enrolling centers. Although it is not required by protocol, sites choosing to perform defibrillation threshold testing will do so according to their institutional standards.

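### Subjects whose CRT-DX implant is attempted but never completed within 30 days of consent are classed as screen failures, so the implant complication rate is measured only in successful implants

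*Protocol article*

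**What the plan says.** Three parts of the protocol article have to be read together.

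- **Who is in the analysis.** The section on protection of human rights, recruitment, and consent states: "Consented subjects will be considered provisionally enrolled until a CRT-DX is implanted successfully". It continues: "Subjects with both signed informed consent and an implanted CRT-DX system are considered enrolled". The exclusion rule has two limbs joined by *or*. It applies to "Provisionally enrolled subjects that exit prior to implant or do not receive a CRT-DX system within 30 days of signing consent". The consequence for both limbs is the same: these people "will be considered screen failures, and will not be included in the analysis population or count toward the 400-subject enrollment goal".
- **What a failed implant is.** The Device implantation section calls an implant unsuccessful if any component "is attempted to be implanted but could not be placed in a stable position", or if the system cannot deliver adequate therapy for a reason attributable to the procedure.
- **What is measured, and in which set.** The fourth secondary objective is "to evaluate the observed major complication rates from device implantation in this population at 12 months". Data analysis, in the text after Figure 2, plans analyses on "both an intention-to-treat and an as-treated basis to account for removal or exchange of the implanted CRT-DX device system".

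The article describes no safety set or attempted-implant set.

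**The concern.** Objective 4 asks how often implanting this system causes major complications. The natural denominator is everyone in whom the procedure was started. As written, membership of the analysis population depends on how the procedure ended. A subject with a lead that could not be placed, a procedural injury, or a death on the table before the system was complete has not received a CRT-DX and so leaves the denominator along with the event.

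The intention-to-treat label adds to the problem. The only departure that the plan lets it absorb is later removal or exchange of a system already in place. A reader who sees that label would assume that failed procedures are counted.

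What is at stake is the safety figure for a two-lead system that the Introduction presents as having fewer complications than a conventional three-lead system. Events not captured at the time are hard to recover later.

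**Working it through.** **Step 1: does the rule reach attempted implants?** The first limb covers exit before implant. The second covers anyone without a system at 30 days, whatever the reason. A subject in whom an implant was started and abandoned, with no later success in the window, meets the second limb. No sentence in the consent or Device implantation sections makes an exception.

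**Step 2: who is affected?** Three groups need separating.
- Exit before any attempt: an ordinary screen failure, no concern.
- Failed first attempt, then a successful implant within 30 days of consent: stays in.
- Attempted, and no system within 30 days: leaves. This is the group at issue.

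A system that is in place but cannot deliver adequate therapy is unclear. One sentence of the consent section requires a successful implant; the next requires only an implanted system.

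**Step 3: the plan's own figure.** The 400 cannot be rebuilt, because the article gives neither an expected proportion nor a target width. Its formula, 1.96 × √[p(1 − p)/400], gives half-widths of 4.9 points at p = 0.5, 4.8 at p = 0.6 and 4.5 at p = 0.7. By definition the 400 excludes failed attempts.

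**Step 4: size of the effect on objective 4.** None of the following inputs is in the article; all are assumed.
- f, share of attempts that fail and leave: 2%, 5%, 8%
- c, complication rate in successful implants: 5%, 8%
- m, risk in failed attempts relative to successes: 1, 2, 4

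Subjects outside the 400 = 400 × f/(1 − f), which is about 8, 21 and 35.

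All-attempts rate = (1 − f)c + f·m·c, so the understatement is f(m − 1)c.

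| f | c | m = 1 | m = 2 | m = 4 |
|---|---|---|---|---|
| 2% | 5% | 5.0% | 5.1% | 5.3% |
| 5% | 5% | 5.0% | 5.25% | 5.75% |
| 8% | 5% | 5.0% | 5.4% | 6.2% |
| 2% | 8% | 8.0% | 8.16% | 8.48% |
| 5% | 8% | 8.0% | 8.4% | 9.2% |
| 8% | 8% | 8.0% | 8.64% | 9.92% |

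The understatement runs from 0 (equal risk) to 0.08 × 3 × 0.08 = 1.92 points. For scale, the half-width at n = 400 is 1.96 × √(0.05 × 0.95/400) = 2.1 points at 5% and 1.96 × √(0.08 × 0.92/400) = 2.7 points at 8%.

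**Step 5: the clinical composite score.** If every failed attempt counted as not improved, an improvement rate p would become p(1 − f). With p assumed at 60–70%, the fall is p × f: 1.2–1.4 points at f = 2%, 3.0–3.5 at 5% and 4.8–5.6 at 8%. This is the range that a sensitivity analysis would show, not an error in the primary estimate.

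**The case against.** The other side has several good points.

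- **The implanted-only population is disclosed.** The Objectives frame the primary question for subjects implanted with the system, and the sample size section counts implanted subjects. A reader might infer that the composite-score result is therefore invalid. The article does not support that: it is a legitimate estimate for successful implants. Only the label misleads.
- **The label matters less here than in a randomised trial.** There is no allocated comparison to protect, and the article says what its two sets are for. That stands, but the term still suggests that failed procedures are included.
- **Failed attempts are not invisible.** A reader might infer that these subjects cannot be described, or that an implant success rate cannot be reported. Neither follows. General considerations places quality of life, walk test, NYHA class, rhythm and history before implant, and Table 1 uses NYHA class and walk distance as criteria after consent. Baseline data collection limits only a further list to fully enrolled subjects. Failed attempts could be counted, and Figure 1, which might show them, is not available.
- **The full protocol or analysis plan may hold a separate safety set.** It may, and nothing says that procedural events in provisional subjects go uncollected. However, the article states the exclusion without qualification, so a set that kept these subjects would need this sentence changed. This is a stated rule rather than an omitted detail.
- **The size is assumed.** This stands in full. Every understatement in the table lies inside the half-width for its own complication rate. A shift in one direction is still not something that a confidence interval allows for.

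**Conclusion.** The point holds in a limited form. As written, objective 4 omits procedural complications and deaths in subjects who never receive a system within 30 days of consent, and the intention-to-treat set is a successfully implanted set.

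A low bias in the complication rate depends on failed attempts carrying more risk than successful ones. That is a reasonable inference which the article does not state; with equal risk there is no bias. On the assumed inputs the understatement is 0 to about 1.9 percentage points. It would be wrong to read this as a demonstrated bias, as the loss of every failed first attempt, or as a wrong figure in the article.

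This is a should-fix rather than a must-fix. The objective is secondary and descriptive, secondary analyses are declared exploratory, and the results are described as hypothesis generating.

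**What to change.** 1. Limit screen failure to subjects who exit before any implant attempt.
2. Define an implant-attempted set: every consented, eligible subject in whom a CRT-DX implant procedure is started. Use it for objective 4 and for an implant success rate with an exact 95% confidence interval.
3. Collect procedure-related events in failed attempts through a short, stated window after the procedure.
4. Keep the composite score in the implanted population, but call that set successfully implanted rather than intention-to-treat. Add a sensitivity analysis that counts failed attempts as not improved.
5. State whether a system that is in place but judged unsuccessful counts as enrolled.

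The cost is a change of wording and a short form for a small number of subjects who have already consented (about 8 to 35 on the assumed failure shares). The complication rate may look slightly less favourable. The 400 implanted-subject target need not change.
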